## Abstract

**Introduction:** Remimazolam is an ultra-short-acting benzodiazepine sedative agent commonly used in general anesthesia, procedural sedation, and intensive care unit (ICU) sedation. This study aimed to explore the efficacy and safety of remimazolam versus propofol for the induction and maintenance of general anesthesia in preschool-age children undergoing elective surgery.

**Methods and analysis:** In this multicenter, randomized, single-blind, positive-controlled non-inferior clinical trial, one hundred ninety-two children aged 3–6 years will be randomly allocated as a 3:1 ratio into two groups: Group R with an intravenous dose of remimazolam 0.3 mg/kg for the induction of anesthesia followed by a constant infusion rate of remimazolam 1–3 mg/kg/h to maintain anesthesia, and Group P with an intravenous dose of propofol 2.5 mg/kg for the induction of anesthesia followed by a constant infusion rate of propofol 4–12 mg/kg/h to maintain anesthesia. The primary outcome will be the rate of the successful induction and maintenance of anesthesia. The secondary outcomes will include the time to LoC, the Bispectral Index (BIS) value, awakening time, extubation time, post-anesthesia care unit (PACU) discharge time, usage of additional sedative drugs during the induction period, usage of remedial drugs in PACU, emergence delirium, pain in PACU, behavior scores at day 3 after surgery, parental and anesthesiologists’ satisfaction, and adverse events.

**Ethics and dissemination:** This study has been approved by the ethics review boards at all participating hospitals. The Ethics Committee of the Second Affiliated Hospital and Yuying Children’s Hospital of Wenzhou Medical University (Reference No. LCKY 2020-380, November 13, 2020) is the central ethics committee.

**Clinical Trial Registration:** Chinese clinical trial registry, identifier ChiCTR2100053468 (22 November 2021)

## 1 Introduction

As undergoing invasive operation and surgery is a stressful and traumatic experience for children, general anesthesia has been the anesthesia regimen of choice in pediatric patients (Cavuoto et al., 2014). The previous study has explored the tight relationship between inhalational anesthesia and postoperative behavioral disturbance incarnated as emergence agitation (EA) or emergence delirium (ED) in pediatric patients (Urits et al., 2020). The mask induction of volatile anesthetic could further aggravate anxiety, and even bring about long-term psychological trauma. Despite the fact that the establishment of peripheral venous access is an invasive procedure before anesthesia induction, fear and anxiety is significantly reduced when accompanied by the parents and some children can even be very cooperative. Therefore, the mainstream view is that total intravenous anesthesia (TIVA) was preferred over inhalational anesthesia (Lauder, 2015).

Among all intravenous anesthetic agents, propofol is the most popular sedative agent used for intravenous induction and maintaining the effects of general anesthesia in pediatric patients by virtue of its advantages in rapid onset, short duration of action, impressive speed and quality of recovery, minimization of ED, decrement of laryngospasm and bronchospasm, and curtailment of postoperative nausea and vomiting (PONV) (Chidambaran et al., 2015; Gentili, 2020). Despite these positive attributes, shortcomings comprising pain on intravenous injection, anaphylaxis, mitochondrial diseases, and propofol-related infusion syndrome (PRIS) have selectively restricted its further application in pediatric patients (Chidambaran et al., 2015). The important point to remember is that pain on intravenous injection of propofol has become the most common adverse effect. Although addition of the local anesthetic lignocaine to propofol in conjunction with use of a propofol emulsion containing medium and long chain triglycerides alleviates the pain, about 35% of pediatric patients still experience pain (Varghese et al., 2010; Jalota et al., 2011). Children who receive a single dose of propofol 1–3 mg/kg for induction usually experience brief apnea, which if not addressed promptly is most likely to develop severe hypoxemia. Moreover, propofol is mainly biotransformed by glucuronidation in the liver and excreted by the kidneys (Al-Jahdari et al., 2006), and the hepatic and renal functions in children are not yet mature enough to facilitate this process. In order to provide safer and smoother anesthesia for pediatric patients, much attention has been devoted to the search for more desirable sedatives.

Remimazolam, a novel ultra-short-acting benzodiazepine, is currently approved as an intravenous agent in multiple countries for use in general anesthesia, procedural sedation, and longer-term sedation in adults, including intensive care (Keam, 2020). It has a high specificity and affinity for the brain benzodiazepine site on the gamma-aminobutyric acid type A (GABAA) receptor to potentiate the action of the inhibitory neurotransmitter without appreciable affinity for any of the other receptor sites (Kilpatrick et al., 2007; Keam, 2020). In contrast to midazolam, remimazolam as a typical ‘soft drug’ (Buchwald, 2020) has the same ester linkage as remifentanil, which leads to rapid biotransformation in the body by widespread tissue esterases to a pharmacologically inactive carboxylic acid metabolite (CNS7054) (Kilpatrick et al., 2007). As a result of its organ-independent metabolism profile, the pharmacokinetics of remimazolam are not subject to any stage of renal impairment, and mild or moderate hepatic impairment (Stöhr et al., 2021). Remimazolam was clinically demonstrated to produce high clearance (CL), faster onset and offset rates than midazolam, and predictable sedation effects over a wide dose range without significant cardiovascular or respiratory depression in two phases I studies (Antonik et al., 2012; Schüttler et al., 2020), in which volunteers received remimazolam as intravenous single ascending dose administration or constant intravenous infusion, respectively. Pharmacokinetic/pharmacodynamic modeling supports the observation of time-dependent change in remimazolam CL that is not related to cumulative remimazolam dose within 24 h of continuous dosing (Zhou et al., 2020). The sedative effect of remimazolam is completely antagonized by flumazenil as a benzodiazepine receptor antagonist (Chen et al., 2020b). These characteristics may reduce the risk of oversedation and rebound sedation under these circumstances of chronic infusions or higher doses in pediatric patients.

Considering the properties of non-irritating, rapidly-acting, short half-life, acceptable and predictable level of sedation, fast emergence from anesthesia, non-dependence on liver and kidney metabolism, minimal residual sedation, inappreciable side effects associated especially with cardiovascular and respiratory depression at usual dosage, and available specific antagonist, remimazolam appears to be suitable for use in children. To date, a search of the literature revealed two case reports of successful remimazolam-based anesthesia for a pediatric patient—one with Duchenne muscular dystrophy (Horikoshi et al., 2021) and the other receiving general anesthesia under intraoperative direct cortical MEP monitoring due to supratentorial glioma (Kamata et al., 2022)— and a clinical trial of remimazolam for sedation in pediatric patients undergoing magnetic resonance imaging (Shioji et al., 2022). Nevertheless, there has been a notable deficiency of empirical randomized clinical trials focusing particularly on the use of remimazolam for general anesthesia in pediatric patients. The primary purpose of this study will be to obtain data that will help to explore the efficacy and safety of remimazolam versus propofol for induction and maintenance of general anesthesia in preschool-age children undergoing elective surgery.

## 2 Methods

### 2.1 Study design

This trial will be designed as a multicenter, single-blind, non-inferior randomized clinical trial to assess the efficacy and safety of remimazolam versus propofol for the induction and maintenance of general anesthesia in children undergoing elective surgery conducted at three Chinese medical centers (The Second Affiliated Hospital and Yuying Children’s Hospital of Wenzhou Medical University, the Children’s Hospital of Chongqing Medical University, Hunan Children’s Hospital). The protocol was approved by the ethics review boards at all participating hospitals and registered with the Chinese Clinical Trial Registry (ChiCTR2100053468, 22 November 2021). The trial is currently in the recruitment phase. Before inclusion, written informed consent will be obtained from their parents or legally authorized representatives of pediatric patients.

### 2.2 Participants

#### 2.2.1 Inclusion criteria

·Aged 3–6 years.·American Society of Anesthesiologists (ASA) physical status I or II.·A normal range of weight and body mass index (BMI) 14–25 kg/m^2^.·Booked for elective surgery (except cardiothoracic, neurosurgical or hepatic surgery) under general anesthesia with endotracheal intubation.·The informed consent signed by parents or legally authorized representatives.

#### 2.2.2 Exclusion criteria

·Requiring special care or supervision of court/social welfare institutions.·Undergoing general anesthesia within 14 days before randomization.·Participating in clinical trials of other drugs within 3 months prior to screening.·In combination with other forms of anesthesia (such as inhalation anesthesia, epidural anesthesia, subarachnoid anesthesia, regional block, etc.) between entry into the operating room until the end of the operation.·Existing other serious illnesses with severe cardiovascular diseases, critical anemia, liver dysfunction (aspartate aminotransferase (AST) and/or alanine aminotransferase (ALT) ≥1.5 upper limit of normal (ULN), total bilirubin (TBIL) ≥ULN), renal dysfunction (serum creatinine and/or urea nitrogen > ULN), neurological disorders including cognitive dysfunction or epilepsy or acute angle-closure glaucoma (AAGG).·Complicated with the difficulty of respiratory management (grade III or IV Modified Mallampati Score) or preexisting abnormal medication behavior.·Suspected to be allergic or contraindicated to benzodiazepines, propofol or drugs specified in this trial (sufentanil citrate, cis-atracurium, remifentanil hydrochloride, ketorolac tromethamine, neostigmine mesylate or atropine sulfate).·Not suitable for participating in this clinical trial judged by the investigator.

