Before anesthesia induction, peripheral venous access will be established and the following vital signs will be monitored throughout the study: continuous electrocardiogram (ECG), heart rate (HR), respiratory rate (RR), pulse oxygen saturation (SpO_2_), and non-invasive blood pressure (NIBP) which will be adjusted by measuring at 1-min intervals until achieving endotracheal intubation and every 5min thereafter. The Bispectral Index (BIS, Aspect Medical Systems-Covidien) pediatric sensor strip will be applied on the forehead of every child, and the BIS value will be recorded before the dose, at LoC, after tracheal intubation and thereafter at 5-min intervals. Subsequently, all pediatric patients will be pre-oxygenated for several minutes in 100% oxygen at a flow rate of 3 L/min followed by a single dose of fentanyl 3 μg/kg (Yichang Humanwell Pharmaceutical, China) intravenously. About 3 min later, all pediatric patients will randomly receive an initial intravenous dose of remimazolam 0.3 mg/kg in Group R or propofol 2.5 mg/kg in Group P for the induction of anesthesia, the injection time ≤60s. The investigator will administer an additional intravenous dose of remimazolam 0.1 mg/kg in Group R or propofol 1.0 mg/kg in Group P under such condition that the child will not achieve the loss of consciousness (LoC: MOAA/S score ≤1) within 60s, the injection time ≤30s. In both groups, the additional dose will be limited to single-use only. If LoC still does not occur within 1 min after the additional dose, propofol 1.0 mg/kg as the remedial sedative drug will be administered repeatedly by intravenous injection until MOAA/S score ≤1, in which general anesthesia will be maintained using isoflurane inhalation instead of propofol or remimazolam.

After reaching LoC without the use of the remedial sedative drug, the researcher will immediately begin taking an intravenous infusion of remimazolam at an initial rate of 2 mg/kg/h in Group R or propofol at an initial rate of 8 mg/kg/h in Group P and remifentanil (Yichang Humanwell Pharmaceutical, China) at an initiation rate of 0.25 μg/kg/min in both groups, while administering cis-atracurium 0.2 mg/kg intravenously. Tracheal intubation will be facilitated to provide assisted ventilation after approximately 3 min.

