#### 2.4.3 Maintenance of general anesthesia

After tracheal intubation is completed, parameters of mechanical ventilation using volume-controlled or pressure-controlled ventilation mode with 50% oxygen/air mixture will be set according to age and ideal body weight to maintain PetCO2 between 35 and 45 mmHg. Anesthesia will be maintained with a constant infusion rate of remimazolam 1–3 mg/kg/h in Group R or propofol 4–12 mg/kg/h in Group P, and remifentanil 0.1–0.5 μg/kg/min in both groups.

The infusion rate of drugs will be adjusted within the prescribed maintenance dose range in the context of the changing intensity of surgical stimuli as primary guidance and the BIS value as secondary guidance to maintain an appropriate depth of anesthesia. Remedial sedative and/or analgesic drugs will be given to children suffering from an inadequate depth of anesthesia defined as the appearance of at least one of the following signs: patient movement, sweating, tears, hypertension and tachycardia (systolic blood pressure (SBP) and HR exceeding 25% of the baseline value for more than 5min), or clear and substantial elevations in SBP or HR, followed by discontinuing the investigational drugs and switching to continuous inhalation of isoflurane. The choice of remedial sedative and/or analgesic medications and dosage will be determined by the investigator. If hemodynamic instability persists in either group, additional vasoactive agents (e.g., esmolol or urapidil) will be administered at the investigator’s discretion. In both groups hypotension (SBP <70 mmHg + (2 x age in years) for a further 5 min) and bradycardia (HR < 70 bpm for a further 5 min) will be treated with ephedrine/phenylephrine and atropine, respectively, and the investigator will decide whether to discontinue the study drugs If necessary.

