Fentanyl 1 μg/kg as an additional dose will be given as needed each time intravenously prior to the anticipated appearance of the significantly larger intensity of surgical stimuli during surgery, and the total intraoperative additional fentanyl dose will be limited to a maximum of 5 ug/kg. Intraoperative muscle relaxation will be given as needed by administration of additional doses of cis-atracurium 0.05 mg/kg each time, aiming to serve surgical needs or maintain effective mechanical ventilation, and no additional muscle relaxants will be administered within approximately 30 min prior to termination of surgery. Ketorolac tromethamine 0.5 mg/kg will be administered intravenously in a usual manner approximately 30 min before termination of surgery, and local infiltration anesthesia, nerve block or sacral anesthesia will be implemented if clinically indicated after surgery for postoperative analgesia. The type, concentration, and dose of local anesthetic will be at the discretion of the investigator. Residual muscle relaxation will be antagonized as required with neostigmine 0.03 mg/kg and atropine 0.015 mg/kg at the end of surgery.

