#### 2.4.4 Recovery from general anesthesia

All the drugs will be discontinued at the end of the surgery. A child who has regular spontaneous breathing and recovery of airway reflexes will be extubated and transferred to the post-anesthesia care unit (PACU) for continuing regular anesthesia monitoring, where an attending anesthesiologist who will be unaware of trial grouping will assess the level of sedation, ED, and pain.

After removal of the investigational drugs, MOAA/S scores will be assessed every 5 min for at least 40 min until 3 consecutive MOAA/S scores of 5. In group R, as long as no arousal occurs after 1 h from the end of remimazolam administration, 0.2 mg flumazenil will be given and a dose of 0.1 mg will be repeated as needed. ED and pain in PACU individually will be evaluated using the Pediatric Anesthesia Emergence Delirium (PAED) scale (Sikich and Lerman, 2004) (Supplementary Table S2)—a reliable tool in the diagnosis of ED and the face, legs, activity, cry and consolability (FLACC) scale (Crellin et al., 2018) (Supplementary Table S3)—a validated pain measurement tool for children aged 2 months to 7 years. Both scales will be recorded every 5 min for at least 30 min after the arrival of PACU. PAED scores ≥10 will be considered a diagnosis of ED and PAED scores ≥15 will be defined as a severe ED. A child considered to have developed delirium or moderate and severe pain (FLACC scale >3) will be treated with remedial sedatives and/or analgesic drugs (e.g., propofol or fentanyl) at the attending anesthesiologist’s discretion. The modified Aldrete score will be recorded every 3 min after 3 consecutive MOAA/S scores of 5, and the child will be admitted to discharge from the PACU until 2 consecutive modified Aldrete scores ≥9.

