### 2.5 Outcomes

The primary endpoint will be the incidence of the successful induction and maintenance of anesthesia. Successful anesthesia induction will be defined as LoC being reached without the use of remedial sedative drugs during the induction period. Successful anesthesia maintenance will be defined as neither need for rescue sedative medication nor discontinuity of investigational drugs during the maintenance period.

The secondary endpoints will include 1) time to LoC: the time interval from an initial dose of investigational drugs to the first MOAA/S score ≤1; 2) usage of additional sedative drugs during the induction period; 3) the BIS value before dose, at LoC, after tracheal intubation and during the maintenance of anesthesia (LoC to end of the investigational drugs); 4) awakening time: the time interval from the end of investigational drugs to the first of 3 consecutive MOAA/S scores of 5; 5) extubation time: the time interval from discontinuation of investigational drugs to extubation; 6) the incidence of ED, moderate and severe pain (FLACC scale >3) in PACU; 7) usage of remedial drugs in PACU; 8) PACU discharge time: the time interval from the end of investigational drugs to the first of 2 consecutive modified Aldrete score ≥9; 9) parental and anesthesiologists satisfaction; and 10) the incidence of negative behavior change at day 3 after surgery.

Safety endpoints will include frequency, causality, and severity of adverse events (AEs) in each treatment arm. Grading of AEs will be according to Common Terminology for Adverse Event (CTCAE), Version 5.0 criteria. Injection site pain, fluctuations in blood pressure or heart rate, and the use of vasoactive agents will be recorded. Postoperative nausea and vomiting (PONV), delayed awakening from anesthesia, and respiratory depression will also be collected.

Detailed information about surgery will be collected: name of surgery, length of surgery, intraoperative bleed loss, the total maintenance dose of study drugs (remimazolam or propofol) and remifentanil, total cumulative additional consumption, frequency of fentanyl and cis-atracurium, and usage of perioperative concomitant medication.

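### The allergy exclusion lists sufentanil, which the protocol never gives, and omits fentanyl, which every child receives, and isoflurane, the prescribed replacement agent

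*Protocol article*

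**What the plan says.** The allergy and contraindication criterion in Section 2.2.2 (Exclusion criteria) covers benzodiazepines, propofol and "drugs specified in this trial (sufentanil citrate, cis-atracurium, remifentanil hydrochloride, ketorolac tromethamine, neostigmine mesylate or atropine sulfate". The parenthesis reads as a complete list. It carries no wording that marks it as examples, whereas the exclusion for combined forms of anesthesia in the same section does.

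The procedures and outcomes name these drugs:

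- **Fentanyl.** In Section 2.4.2, pre-oxygenation in all children is "followed by a single dose of fentanyl" at 3 μg/kg. Section 2.4.3 allows further 1 μg/kg doses, and "the total intraoperative additional fentanyl dose will be limited to a maximum of" 5 μg/kg. Section 2.4.4 names it for rescue in the post-anesthesia care unit (PACU), through "analgesic drugs (e.g., propofol or fentanyl". Section 2.5 records "total cumulative additional consumption, frequency of fentanyl and cis-atracurium".
- **Isoflurane.** If induction fails and remedial propofol is needed, "general anesthesia will be maintained using isoflurane inhalation instead of propofol or remimazolam" (Section 2.4.2). If depth is inadequate during maintenance, the study drug is stopped, with "switching to continuous inhalation of isoflurane" (Section 2.4.3).
- **Flumazenil.** In Group R, if the child has not roused 1 h after the infusion ends, "0.2 mg flumazenil will be given and a dose of 0.1 mg will be repeated as needed" (Section 2.4.4).

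Sufentanil appears in none of these sections.

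**The concern.** The purpose of this criterion is to keep out any child who should not be given a drug that the protocol will or may give. For that, the drugs screened and the drugs given have to agree. Here the opioid named for screening is not given, and the opioid given to every child is not named. The volatile agent to which a child must be switched in mid-anesthetic is not named either.

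What is at stake is the safety of children aged 3–6 years and consistent screening across three centers in a trial that Section 2.1 describes as already recruiting. One center may read the general words before the parenthesis as covering fentanyl and isoflurane; another may work through the six names. The mismatch also leaves open which part of the document is wrong, the exclusion list or the opioid in the procedures. The efficacy analysis is not at stake.

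**Working it through.** No alpha, rate or margin enters this point, and the plan gives no figure to reproduce. The check compares the exclusion list with the procedures in both directions.

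**Step 1. From the list to the procedures: is each listed drug given?**

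| Listed in 2.2.2 | Where the procedures give it |
|---|---|
| Cis-atracurium | 2.4.2 (intubation), 2.4.3 (top-up) |
| Remifentanil | 2.4.2 (start of infusion), 2.4.3 (maintenance) |
| Ketorolac | 2.4.3 (about 30 min before the end of surgery) |
| Neostigmine | 2.4.3 (reversal, when required) |
| Atropine | 2.4.3 (bradycardia; reversal) |
| Sufentanil | nowhere |

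Result: 5 of 6 are used and 1 of 6 is not.

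**Step 2. From the procedures to the list: is each relevant drug screened for?**

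| Given in the procedures | Who may receive it | Listed in 2.2.2? |
|---|---|---|
| Remimazolam, propofol | By allocation; propofol also as remedial drug | Yes (benzodiazepines, propofol) |
| Fentanyl | Every child, both groups | No |
| Isoflurane | Any child with failed induction or inadequate depth | No |
| Flumazenil | Group R, no arousal after 1 h | No |

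**Step 3. Exposure to the omitted opioid.** The minimum is the induction dose, 3 μg/kg. Adding the capped intraoperative doses gives 3 + 5 = 8 μg/kg. This excludes any fentanyl given in the PACU. It also excludes any given as a remedial analgesic under Section 2.4.3, where drug and dose are left to the investigator and the relation to the 5 μg/kg cap is not stated. So 8 μg/kg is the total of the scheduled and capped doses, not a firm ceiling.

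**Step 4. Expected exposure to isoflurane.** Section 2.6 assumes 98% success in both groups and plans 192 children, so about (1 − 0.98) × 192 = 3.84, or roughly 4, would fail the primary endpoint. Not every failure need lead to isoflurane: stopping the study drug for hypotension or bradycardia, for example, carries no stated switch. The expected number is therefore small if the 98% holds. Eligibility, however, has to be settled before anyone knows which children these will be.

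**Step 5. Does a listed drug stand in for an omitted one?** Remifentanil would catch a child with a general contraindication to opioids, but not necessarily one specific to fentanyl. No volatile agent is listed, so nothing stands in for isoflurane.

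**The case against.** The strongest reply is that the operative words are broader than the parenthesis. The criterion refers to the drugs specified in the trial, and fentanyl and isoflurane plainly are. An anesthetist takes a history and examines each child at the pre-anesthesia visit (Section 2.4.1), and Section 2.2.2 also lets the investigator exclude any child judged unsuitable. Harm would require an anesthetist who knows of a contraindication to fentanyl or a volatile agent to proceed because the drug is not among six names. This stands as mitigation and is why the practical risk is probably low. It does not make the list right: the parenthesis spells out the general phrase, and spells it out wrongly.

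A second reply is that the list covers routine drugs and leaves contingency drugs out: the vasoactive agents in Section 2.4.3 (ephedrine, phenylephrine, esmolol, urapidil) are missing as well as isoflurane and flumazenil. On that reading the isoflurane omission is a drafting choice. It is fair to say that the isoflurane point is weaker than the fentanyl point. But the list already includes neostigmine, which is given only when required, so conditional use is not a clean dividing line. Isoflurane also differs from the other contingency drugs in being the only maintenance agent the protocol names once the study drug is stopped for failed induction or inadequate depth.

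A third reply is that sufentanil might be chosen as a discretionary rescue analgesic. That would explain its presence only loosely, since no section specifies it, and fentanyl would still be missing.

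Finally, this is a journal article. Whether the mismatch is also in the full protocol used at the sites cannot be seen here. The list is printed in full, however, so condensation does not explain a wrong entry.

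**Conclusion.** The criterion is wrong as written. One of its six named drugs is not used, the opioid given to all 192 planned children is not named, and the prescribed replacement maintenance agent is not named. The flumazenil omission is minor. The pattern suggests that sufentanil was written for fentanyl, but the article does not say so, and only the sponsor can settle it.

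The effect is confined to patient safety and protocol adherence. The primary endpoint, sample size, power and non-inferiority margin are unaffected. How many children with a relevant contraindication would be missed cannot be estimated from the article, and given the safeguards the number may well be nil. The conclusion assumes that the article reproduces the list used for screening. If the full protocol already has it right, only the article needs correcting. The change should be made because the rule concerns the safety of young children and costs almost nothing to correct.

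**What to change.** In Section 2.2.2, replace sufentanil citrate with fentanyl and add isoflurane, so that the named drugs are fentanyl, remifentanil, cis-atracurium, ketorolac, neostigmine, atropine and isoflurane. Adding flumazenil is optional. If the sponsor also wants the remaining contingency drugs covered, a short closing phrase extending the list to any other drug named in Section 2.4 would do it.

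If sufentanil is in fact the intended opioid, leave it in the list and correct Sections 2.4.2, 2.4.3, 2.4.4 and 2.5 instead, with the doses restated for that drug.

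The cost of the first option is a one-line amendment, with a matching change to any screening form in use at the three centers. Because the trial is recruiting, the sites should be told promptly. Sample size and analysis do not change.
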